## Abstract

**Background:**

Early essential newborn care (EENC) is a package of evidence-based and cost-effective interventions delivered around birth mainly including delayed cord clamping, immediate and sustained skin-to-skin contact, and early initiation of exclusive breastfeeding. EENC is proven effective in promoting breastfeeding and improving women’s and newborns’ health. However, there is little evidence on implementation of EENC on newborns born by cesarean section in China. Therefore, the objective of this study is to assess the effectiveness of EENC intervention on rates of exclusive breastfeeding and early initiation of breastfeeding for cesarean section newborns in China.

**Methods:**

This is a multi-centered, randomized controlled trial conducted in 4 tertiary hospitals in China. A total of 720 eligible women who will receive cesarean section are being randomized into four groups: control group (*n*=180), intervention group 1 (skin-to-skin contact for 30 min, *n*=180), intervention group 2 (skin-to-skin contact for 60 min, *n*=180), and intervention group 3 (skin-to-skin contact for 90 min, *n*=180). The control group will receive routine care, whereas the intervention groups will receive EENC with different duration of skin-to-skin contact. Demographic characteristics, clinical information, and breastfeeding outcomes will be collected. The primary outcome is rates of exclusive breastfeeding and early initiation of breastfeeding, and the secondary outcomes include maternal and neonatal morbidity and admissions.

**Discussion:**

This study will provide evidence of the impact of EENC on improvement of breastfeeding outcomes and maternal and neonatal health for cesarean section newborns in China, and evidence-based recommendation to inform optimal duration of skin-to-skin contact for cesarean deliveries. The results of this study have potential to inform national-level guidelines and policy-making for optimizing EENC implementation for cesarean section newborns.

**Trial registration:**

Chinese Clinical Trial Registry ChiCTR2100048997. Retrospectively registered on 19 July 2021

**Supplementary Information:**

The online version contains supplementary material available at 10.1186/s13063-022-06615-z.

## Background

Deaths before 5 years of age have been estimated to 5.3 million globally in 2018, 47% of which occurred in the neonatal period (the first 28 days of life) [1]. In China, the neonatal mortality rate has been estimated at 4.5‰, accounting for nearly half of the under-five deaths [2]. To reduce preventable neonatal morbidity and mortality and improve women’s and newborns’ health, World Health Organization (WHO) and the United Nations Children’s Fund (UNICEF) jointly developed the Action Plan for Healthy Newborn Infants in the Western Pacific Region (2014–2020) which focused on delivery of early essential newborn care (EENC) [3]. EENC is a package of simple evidence-based and cost-effective interventions delivered around birth including thoroughly drying a newborn immediately after birth, delayed cord clamping, immediate and sustained skin-to-skin contact (SSC), initiating exclusive breastfeeding, and routine care (newborn eye care, vitamin K_1_, immunizations, weighting, and examinations) [3, 4]. Implementation of EENC has been demonstrated to increase rates of exclusive breastfeeding at discharge, 3 months and 6 months of age, and reduce neonatal intensive care unit admissions, admissions with hypothermia and sepsis [5, 6].

Accumulating evidence suggested that SSC contributed to increased exclusive breastfeeding rates on discharge, at 6 months and lower rate of transfer of newborns to the neonatal intensive care unit, regardless of mode of delivery [7–9]. In addition, babies born by cesarean section who received prolonged SSC had similar rates of exclusive breastfeeding at discharge as those born vaginally [4]. WHO recommends SSC for 1 h after birth which was consistent with implications of the Cochrane review [10, 11]. However, a recent cross-sectional observational study from the Western Pacific Region Early Essential Newborn Care Working Group reported a strong dose-response relationship between the duration of SSC and early initiation of breastfeeding through 90 min after birth [4]. Thus, the optimal duration of SSC needs further investigation.

Delayed cord clamping is another important procedure of EENC. A previous randomized controlled trial indicated that delayed cord clamping under cesarean section was associated with lower amount of postpartum bleeding, and increased hemoglobin and hematocrit in newborn heel blood [12]. Compared to those without delayed cord clamping, newborns with delayed cord clamping had decreased mean estimated maternal blood loss and transfusions and reduced prevalence of newborn anemia [13].

In 2016, EENC for vaginal deliveries was introduced in 6 hospitals in China, and afterwards scaled up to 18 counties in four provinces in Western China for pilot study [14, 15]. The study found that exclusive breastfeeding at discharge increased from 43 to 73%, and the average length of the first breastfeeding and the proportion of newborns receiving immediate SSC and prolonged SSC for more than 90 min were significantly increased [14]. To date, studies for EENC focused on newborns born by vaginal delivery in China, while there is limited evidence regarding implementation of EENC on cesarean section newborns. Furthermore, one-in-three (34.9%) births occur by cesarean section in China [16], and most of these babies might be deprived of the benefits of EENC. Therefore, the purpose of this study is to assess the effect of EENC intervention on breastfeeding outcomes and maternal and neonatal health for cesarean section newborns in comparison with the routine care in China. This study will be a parallel-group randomized trial, and participants will be allocated into 4 groups (1 control group and 3 intervention groups according to the duration of SSC) at a 1:1:1:1 ratio.

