## Methods/ design

### Study design

This study is a multi-centered, randomized, open-labeled, superiority trial which is conducted at four tertiary hospitals in four provinces in China: Beijing, Sichuan, Shaanxi, and Ningxia. Four tertiary hospitals involved in our study are listed in Table 1. The study aims to compare the difference of early initiation of breastfeeding rates and exclusive breastfeeding rates among 4 different groups of mother and newborn pairs with full-term elective cesarean section (control group; intervention group 1: SSC for 30 min; intervention group 2: SSC for 60 min; and intervention group 3: SSC for 90 min). A total of 720 eligible pairs of mothers and neonates will be recruited and allocated into 4 groups at a 1:1:1:1 ratio. Figure 1 presents an explicit flow chart of this study. This clinical trial follows the guidelines for randomized clinical trials (SPIRIT checklist (Additional file 1)) [17]. The schedule of enrolment, interventions, and assessments are shown in Table 2.

**Table 1 Tab1:** Study sites involving in this multi-centered randomized controlled study

Study sites	Location	Role
Peking University First Hospital	Beijing	Management and participant
Sichuan Provincial Hospital for Women and Children	Sichuan	Participant
Shaanxi Provincial Maternal and Child Health Care Hospital	Shaanxi	Participant
General Hospital of Ningxia Medical University	Ningxia	Participant

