### Intervention and control groups

Pregnant women will be randomly assigned into one of four groups. The control group will receive only routine care (newborn eye care, vitamin K_1_, immunizations, weighing, and examinations) after birth, whereas the intervention group will receive EENC including delayed cord clamping, immediate and sustained SSC, initiating exclusive breastfeeding, and routine care. The flow chart of EENC for cesarean section is showed in Fig. 2. Delayed cord clamping is defined as cutting umbilical cord until cord pulsations have ceased (approximately 1–3 min after birth) [18]. Immediate and sustained SSC is regarded as placing of the naked baby prone on the mother’s bare chest immediately after birth without separation [10]. Pairs of mothers and newborns in the intervention group 1, intervention group 2, and intervention group 3 will perform SSC for 30 min, 60 min, and 90 min, respectively.

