### Sample size calculation

We calculated the sample size based on the rate of early initiation of breastfeeding, which is one of the primary outcomes in this study. According to our pilot investigation and previous literature [4, 20], the rate of early initiation of breastfeeding is 40% in the control group (receiving routine care), and the rates in the intervention group 1 (receiving EENC with SSC for 30 min), intervention group 2 (receiving EENC with SSC for 60 min), and intervention group 3 (receiving EENC with SSC for 90 min) are supposed to be 60%, 70%, and 80%, respectively. Accounting for multiple comparisons (SSC for 30 min vs. routine care, SSC for 60 min vs. routine care, SSC for 90 min vs. routine care, SSC for 30 min vs. SSC for 60 min, SSC for 30 min vs. SSC for 90 min, SSC for 60 min vs. SSC for 90 min), a level of significance is set to be 0.008 (0.05/6) by using Bonferroni adjustments. For 80% power, the sample size required for each of the control group and the intervention group 1 is 152 participants; the sample size required for each of the control group and the intervention group 2 is 64 participants; the sample size required for each of the control group and the intervention group 3 is 34 participants. The largest sample size group (*n*=152) is selected as the number of recruitment in each group. Considering 15% of loss to follow-up, the number of participants in each group is finally set to be 180 and adds up to a total of 720 participants. One hundred eighty participants will need to be recruited in each of four hospitals, which means that each of the hospital will recruit 45 participants in the control group, intervention group 1, intervention group 2, and intervention group 3, respectively. The sample size calculation was performed using PASS 2011 software (NCSS, Kaysville, UT, USA).

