### Analysis plan

Baseline characteristics of participants will be presented as mean (standard deviation) for continuous variables and number (percentage) for categorical variables. Data will be analyzed on an intention-to-treat basis to compare primary and secondary outcomes in four groups. The chi-square test or one-way analysis of variance will be used to compare the characteristics and rates of exclusive breastfeeding and early initiation of breastfeeding, and maternal and neonatal outcomes among the 4 groups (control group, intervention group 1, intervention group 2, and intervention group 3). For missing data, we will use multiple imputation to obtain complete datasets. All the statistical analyses will be conducted using SPSS 20.0 statistical software (SPSS Inc., Chicago, Illinois). A two-sided *P* value <0.05 indicated significance.

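### The stated purpose is EENC against routine care, but no comparison combines the three EENC arms against control; this costs little for early initiation and loses power for outcomes such as postpartum hemorrhage

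*Protocol article*

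**What the plan says.** The Background gives the purpose: "the purpose of this study is to assess the effect of EENC intervention on breastfeeding outcomes and maternal and neonatal health", "in comparison with the routine care in China". The Abstract and the Discussion give the same objective for the breastfeeding outcomes. The Study design section words the aim differently: "The study aims to compare the difference of early initiation of breastfeeding rates and exclusive breastfeeding rates among 4 different groups". The Abstract, Background and Discussion also make the best SSC duration a question of the trial.

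Under Intervention and control groups, "the intervention group will receive EENC including delayed cord clamping, immediate and sustained SSC, initiating exclusive breastfeeding, and routine care". The three intervention arms differ only in SSC duration (30, 60 or 90 min). Control receives routine care alone.

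The Sample size calculation lists six pairwise comparisons. Three are against control: "SSC for 30 min vs. routine care, SSC for 60 min vs. routine care, SSC for 90 min vs. routine care". The other three are between durations. Its significance level is 0.008 (0.05/6).

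The Analysis plan names a chi-square test or one-way analysis of variance for both breastfeeding outcomes and for "maternal and neonatal outcomes among the 4 groups (control group, intervention group 1, intervention group 2, and intervention group 3"). Significance there is two-sided 0.05.

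**The concern.** The trial asks two questions: whether the EENC package beats routine care, and which SSC duration is best. The named analysis gives no single estimate for the first. The four-group test has no direction and can be significant because of differences between durations alone. The pairwise comparisons use 180 EENC pairs at a time, although 540 receive the package.

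This matters most where the active component is common to all EENC arms. The Background cites a trial in which "delayed cord clamping under cesarean section was associated with lower amount of postpartum bleeding", and every EENC arm has delayed cord clamping. If hemorrhage responds to clamping, splitting the EENC arms by SSC duration discards information. A real package effect could be reported as a scatter of inconclusive duration results.

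The labels also need care. The comparison called 30 min of SSC against routine care contains cord clamping and breastfeeding initiation as well, so a difference there belongs to the package.

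**Working it through.** **1. The plan's own figure.** Inputs from the Sample size calculation: 40% in control; 60%, 70% and 80% in the EENC arms; two-sided 0.008; 80% power.

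n = [z(α/2)·√(2p̄(1−p̄)) + z(β)·√(p₁(1−p₁)+p₂(1−p₂))]² / (p₁−p₂)²

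For 40% against 60%: [2.652·√0.5 + 0.842·√0.48]² / 0.04 = 2.458² / 0.04 ≈ 151.1, so 152, as stated. The other two comparisons give 66 and 36, against 64 and 34 in the article, within two participants. Loss: 152/0.85 = 178.8, so 179, set to 180.

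**2. Early initiation at the planned rates.** Power of each control comparison at 0.008:

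| EENC arm | 152 per arm | 180 per arm |
|---|---|---|
| 30 min (60%) | 80% | 88% |
| 60 min (70%) | 99.7% | 99.9% |
| 90 min (80%) | >99.9% | >99.9% |

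The combined contrast (mean 70% against 40%) at 0.05 also exceeds 99.9%, so leaving it out costs almost nothing here.

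**3. Outcomes with an effect common to all EENC arms.** The article gives no hemorrhage rate and no SD for hemoglobin, so the rates and shifts below are assumptions. All use 180 per arm.

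Two proportions: power = Φ[(d − z(α/2)·SE₀)/SE₁], with SE₀ from the pooled rate and SE₁ from the separate rates. For 10% against 5%, 180 against 540, at 0.05: pooled rate 0.0625, SE₀ = 0.02083, SE₁ = 0.02425, (0.05 − 1.96·0.02083)/0.02425 = 0.378, power 64.7%. One pair (180 against 180) at 0.008: SE₀ = 0.02776, SE₁ = 0.02764, (0.05 − 2.652·0.02776)/0.02764 = −0.855, power 19.6%. Four-group chi-square, 3 df: noncentrality 180·Σ(pᵢ−p̄)²/[p̄(1−p̄)] = 5.76, power 50.0%.

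Continuous outcome, shift δ in SD units: combined power = Φ[δ/√(1/180+1/540) − 1.96]. For δ = 0.25 this is Φ(2.905 − 1.96) = 82.8%. One pair: Φ(2.372 − 2.652) = 39.0%. Four-group F test with 3 and 716 df: noncentrality 180·0.75·0.25² = 8.44, power 67.7%.

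| Assumed effect, same in all EENC arms | Combined, 0.05 | Four-group, 0.05 | One pair, 0.008 |
|---|---|---|---|
| Hemorrhage 6% vs 3% | 45.7% | 30.5% | 10.0% |
| Hemorrhage 10% vs 5% | 64.7% | 50.0% | 19.6% |
| Hemorrhage 15% vs 8% | 75.4% | 62.4% | 28.3% |
| Shift 0.20 SD | 64.2% | 47.0% | 22.5% |
| Shift 0.25 SD | 82.8% | 67.7% | 39.0% |
| Shift 0.30 SD | 93.6% | 84.3% | 57.7% |

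Part of the gap to the last column is the stricter level, and the article does not say whether 0.008 applies to secondary outcomes. At 0.05, one pair with a 0.25 SD shift has 66%, still below 83%.

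**4. A significant four-group test need not mean a package effect.** Assume 50% in control and 40%, 50% and 60% in the EENC arms, so the EENC mean equals control. Noncentrality is 14.4, and the four-group test rejects about 90% of the time.

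**5. Where the combined contrast gains or loses on a breastfeeding rate** (assumed rates: control, 30, 60, 90 min):

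| Rates | Combined | Four-group |
|---|---|---|
| 40/50/50/50% | 65% | 47% |
| 40/48/52/56% | 80% | 76% |
| 40/45/50/60% | 78% | 93% |
| 40/40/50/60% | 65% | 97% |

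The second row keeps the planned 20:30:40 gradient at a smaller size. The last two show the loss when the benefit sits mainly at longer durations.

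**The case against.** The strongest reply is that each arm-versus-control comparison is already a complete randomized test of the EENC package at one duration, and that for early initiation each is adequately powered at the adjusted level. This stands. A reader might infer that the main objective is tested only in fragments; the documents do not support that.

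The Study design section words the aim as a four-group comparison, and duration is a declared question, so the four-group test answers a stated aim. This also stands. It does not supply the package estimate that the Background describes.

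The gain from combining rests on similar effects across arms, while the planning rates rise with duration. This is right for breastfeeding, and step 5 shows that the combined contrast can lose heavily. It is a sound reason not to put that contrast first as a gate for the primary outcomes. The only exclusive breastfeeding figures given, 43% rising to 73% in a vaginal-delivery pilot, would leave over 99% power under any of these tests if they held in all EENC arms.

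Two further stronger readings fail. The Background links cord clamping to maternal bleeding, blood loss and transfusion, but its hemoglobin result is measured in the newborn; it does not link clamping to maternal hemoglobin or mention bilirubin. And the article never calls control a zero-minute SSC arm or plans a trend that includes it. Misattribution is a risk to guard against, not a stated error.

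Finally, an analysis plan that is not shown may contain the combined contrast. That is possible. But the article does name its test for every outcome, and that test does not match the stated purpose.

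**Conclusion.** The point holds as a gap of moderate weight between purpose and analysis. No stated figure is wrong, and early initiation at the planned rates is practically unaffected. The loss is real for outcomes on which the three EENC arms should act alike, first of all postpartum hemorrhage. Across the assumed effects in step 3, the combined contrast has about 9 to 17 percentage points more power than the four-group test (93.6 − 84.3 = 9.3 at the least; 64.2 − 47.0 = 17.2 at the most).

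This rests on assumed rates and shifts, 180 analysed per arm and equal effects across the EENC arms. Including maternal hemoglobin is an inference from its likely dependence on blood loss, which the article does not state. Exclusive breastfeeding at discharge lies in between: the article gives no planning rate or power for it, and the contrast helps or hurts according to how steeply the effect rises with duration.

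**What to change.** In the Analysis plan:

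- Prespecify a contrast of the three EENC arms combined (540) against control (180), and state its significance level and place in the multiplicity scheme.
- Make it the main comparison for postpartum hemorrhage and maternal hemoglobin.
- For early initiation and exclusive breastfeeding, report it as a supporting package estimate beside the arm-specific rates. It should neither replace nor gatekeep the arm-versus-control tests.
- Draw duration conclusions only from comparisons among the 30, 60 and 90 min arms, and attribute differences between control and any EENC arm to the package.

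This is a change of analysis wording, with no new data or participants, and should be fixed before outcomes are seen by arm. The cost is that the combined estimate averages over durations and loses power if only the longer ones work, which is why the arm-specific results must stand beside it.

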## Methods/ design

### Study design

This study is a multi-centered, randomized, open-labeled, superiority trial which is conducted at four tertiary hospitals in four provinces in China: Beijing, Sichuan, Shaanxi, and Ningxia. Four tertiary hospitals involved in our study are listed in Table 1. The study aims to compare the difference of early initiation of breastfeeding rates and exclusive breastfeeding rates among 4 different groups of mother and newborn pairs with full-term elective cesarean section (control group; intervention group 1: SSC for 30 min; intervention group 2: SSC for 60 min; and intervention group 3: SSC for 90 min). A total of 720 eligible pairs of mothers and neonates will be recruited and allocated into 4 groups at a 1:1:1:1 ratio. Figure 1 presents an explicit flow chart of this study. This clinical trial follows the guidelines for randomized clinical trials (SPIRIT checklist (Additional file 1)) [17]. The schedule of enrolment, interventions, and assessments are shown in Table 2.

**Table 1 Tab1:** Study sites involving in this multi-centered randomized controlled study

Study sites	Location	Role
Peking University First Hospital	Beijing	Management and participant
Sichuan Provincial Hospital for Women and Children	Sichuan	Participant
Shaanxi Provincial Maternal and Child Health Care Hospital	Shaanxi	Participant
General Hospital of Ningxia Medical University	Ningxia	Participant

**Fig. 1 Fig1:**
[figure not shown]
Flow chart of the study

**Table 2 Tab2:**
[figure not shown]
Schedule of enrolment, interventions, and assessments of this study

### Study participants

Among pregnant women who will receive cesarean delivery, eligible women and their newborns who meet the inclusion criteria and none of the exclusion criteria will be recruited in this study.

#### Inclusion criteria

Inclusion criteria are as follows:Gestational weeks ≥ 37 weeksElective cesarean sectionSingleton pregnancyEpidural anesthesia, or subarachnoid block anesthesia, or combined spinal-epidural anesthesiaAble to provide written informed consent

#### Exclusion criteria

Exclusion criteria are as follows:Serious pregnancy complications such as placenta previa, placenta accreta spectrum, and eclampsiaNeonatal complications such as neonatal asphyxia and neonatal birth defectsUnable to breastfeedDifficulty in undergoing skin-to-skin contactInfectious diseases such as hepatitis B, syphilis, and HIV

### Randomization and blinding

The randomization sequences are generated by the biostatistician using the random number sequence generator function in SAS software version 9.2 (SAS Institute, Cary, NC), with stratification by study sites. Participants will be assigned a randomization code according to their sequential numbers and randomly allocated into one of four groups with a 1:1:1:1 ratio in the operating room. Due to the nature of EENC interventions, blinding of participants, obstetricians, nurses/midwives, and intraoperative research staff is infeasible.

### Recruitment

In four study sites, obstetricians and midwives introduce the contents, advantages, and precautions of EENC to pregnant women and their families at prenatal visits and before delivery, including delayed cord clamping, immediate and continuous SSC, and early initiation of breastfeeding, so that pregnant women and their families could understand and cooperate in the implementation of EENC. Also, participants and their families will be educated to breastfeeding and early identification of neonatal risk signs (including breathing and skin color) and health care contents for newborns (including bathing, umbilical care, and vaccination). Among pregnant women who will receive cesarean section, eligible women will be identified and informed of procedures of EENC before cesarean section by obstetricians and midwives, and given the choice of participation on voluntary basis on the day of scheduled elective cesarean delivery. After informed consent is signed, research staff will randomly assign participants into one of four groups with a pre-generated randomization code. In addition to introducing the advantages and benefits of EENC to pregnant women and their families that have mentioned above, there will be no specific plans to promote participant retention. During skin-to-skin contact, midwives and researchers will emphasize the advantages and benefits of EENC and keep encouraging participants in order to help them to complete this process. All of the participants will be free to withdraw from the study at any time if they wish.

